| 52. Frequently had no visual reaction to a “new” person                                                                                                                                                                                                                                          | 3            |   |   |   |   |
| Gets involved in complicated “rituals” such as lining things up (for example, the child must walk a specific route, or before eating, sleeping, or doing something, they must place certain objects in certain positions or perform certain actions. Otherwise, they refuse to sleep, eat, etc.) |              |   | 4 |   |   |

|                                                                            |   |  |   |   |   |
|----------------------------------------------------------------------------|---|--|---|---|---|
| Is very destructive (toys and household items are quickly broken)          |   |  | 2 |   |   |
| A developmental delay was identified at or before 30 months of age         |   |  |   |   | 1 |
| Uses at least 15 but less than 30 spontaneous phrases daily to communicate |   |  |   | 3 |   |
| 57. Stares into space for long periods of time                             | 4 |  |   |   |   |
| Total :                                                             |   |  |   |   |   |
| Overall Total:                                                      |   |  |   |   |   |
| Comments:                                                           |   |  |   |   |   |

Structure of the Scale and Scoring Standards: The ABC (Autism Behavior Checklist) consists of 57 items, covering symptoms related to sensory, behavioral, emotional, language, and self-care aspects of individuals with autism. These can be summarized into 5 factors:

- Sensory (S) (9 items, total of 26 points)
- Relating (R) (12 items, total of 38 points)
- Body and Object Use (B) (12 items, total of 38 points)
- Language (L) (13 items, total of 31 points)
- Social and Self-Help (S) (11 items, total of 25 points)

Each item is assigned a different score based on its weight in the scale, ranging from 1 to 4 points. For any item, as long as the child exhibits that behavior, regardless of the severity, the corresponding score is awarded. The final result is determined based on the total score of all items.

Method of Evaluating Results:

- Total score < 53 points: Negative for screening
- Total score  $\geq 53$  and  $\leq 67$  points: Positive for screening
- Total score  $\geq 68$  points: Can assist in diagnosing autism.

The higher the total score on the scale, the more severe the behavioral symptoms of autism.

### Appendix 3 – Data Form (CSHQ)

#### Childhood Sleep Habits Questionnaire (CSHQ)

Name: Sex: Age:

Name of Person filling form: Relationship:

Contact:

Date Of Birth: \_\_\_\_Year\_\_\_\_Month \_\_\_\_ Date

Date & time of filling form: \_\_\_\_Year\_\_\_\_Month \_\_\_\_Date

The following statements are about your child's sleep habits and possible difficulties with sleep. Think about the past week in your life when you answer the questions. If last week was unusual for a specific reason, choose the most recent typical week. Unless noted, check Usually if it occurs 5 or 6 times a week, Sometimes if it occurs 2 to 4 times a week, Rarely if it occurs once a week or less than once a week.

#### **BEDTIME**

Write in your child's usual bedtime: Weeknights \_\_\_\_:\_\_\_\_ am/pm

Weekends \_\_\_\_:\_\_\_\_ am/pm

|                                                                                           | Usually
(5-7times
/Week) | Sometimes
(2-4 times
/Week) | Rarely
(0-1 times
/Week) |
|-------------------------------------------------------------------------------------------|--------------------------------|-----------------------------------|--------------------------------|
| 1.Child goes to bed at the same time at night                                             |                                |                                   |                                |
| 2.Child falls asleep within 20 minutes after going to bed.                                |                                |                                   |                                |
| 3.Child falls asleep alone in own bed                                                     |                                |                                   |                                |
| 4.Child falls asleep in parent's or sibling's bed.                                        |                                |                                   |                                |
| 5.Child falls asleep with rocking or rhythmic movements.                                  |                                |                                   |                                |
| 6.Child needs special object to fall asleep (doll, special blanket, stuffed animal, etc.) |                                |                                   |                                |
| 7.Child needs parent in the room to fall asleep.                                          |                                |                                   |                                |
| 8. Child go to bed voluntary at bedtime                                                   |                                |                                   |                                |
| 9.Child resists going to bed at bedtime                                                   |                                |                                   |                                |
| 10. Child struggles at bedtime (cries, refuse to stay in bed etc.)                        |                                |                                   |                                |
| 11. Child is afraid of sleeping in the dark.                                              |                                |                                   |                                |
| 12. Child is afraid of sleeping alone.                                                    |                                |                                   |                                |
| 13. Child is afraid to pass away in sleep.                                                |                                |                                   |                                |

## SLEEP BEHAVIOUR

Child's usual amount of sleep each day: \_\_\_hours \_\_\_mins

(combining nighttime sleep and naps)

|                                                                                   | Usually
(5-7times
/Week) | Sometimes
(2-4 times
/Week) | Rarely
(0-1 times
/Week) |
|-----------------------------------------------------------------------------------|--------------------------------|-----------------------------------|--------------------------------|
| 14. Child sleeps too little                                                       |                                |                                   |                                |
| 15. Child sleeps too much                                                         |                                |                                   |                                |
| 16. Child sleeps the right amount                                                 |                                |                                   |                                |
| 17. Child's sleep quality is good                                                 |                                |                                   |                                |
| 18. Child's sleep quality is consistent                                           |                                |                                   |                                |
| 19. Child wets the bed at night                                                   |                                |                                   |                                |
| 20. Child talks during sleep                                                      |                                |                                   |                                |
| 21. Child is restless and moves a lot during sleep                                |                                |                                   |                                |
| 22. Child sleepwalks during the night                                             |                                |                                   |                                |
| 23. Child sleep in the same room as the parents (or caregiver)                    |                                |                                   |                                |
| 24. Child sleep in the same bed as the parents (or caregiver)                     |                                |                                   |                                |
| 25. Child moves to someone else's bed during the night (Parents, brother, sister) |                                |                                   |                                |
| 26. Child has physical aches and pain during sleep                                |                                |                                   |                                |
| If yes, location on body:                                                         |                                |                                   |                                |
| 27. Child grinds teeth during sleep                                               |                                |                                   |                                |
| 28. Child snores badly                                                            |                                |                                   |                                |
| 29. Child seems to stop breathing during sleep                                    |                                |                                   |                                |
| 30. Child snorts and/or gasps during sleep                                        |                                |                                   |                                |
| 31. Child has trouble sleeping away from home (visiting relatives/vacation)       |                                |                                   |                                |
| 32. Child complains of sleeping poorly                                            |                                |                                   |                                |
| 33. Child awakens during the night screaming, sweating and inconsolable           |                                |                                   |                                |
| 34. Child awakes alarmed by a frightening dream                                   |                                |                                   |                                |

## WAKING DURING THE NIGHT:

|                                                                           | Usually
(5-7times
/Week) | Sometimes
(2-4 times
/Week) | Rarely
(0-1 times
/Week) |
|---------------------------------------------------------------------------|--------------------------------|-----------------------------------|--------------------------------|
| 35. Child awakes once during the night                                    |                                |                                   |                                |
| 36. Child awakes more than once during the night                          |                                |                                   |                                |
| 37. Child need help to fall back asleep after waking up at night          |                                |                                   |                                |
| 38. Duration of time child wakes up at night is usually:    hours    mins |                                |                                   |                                |

## MORNING WAKING:

Write in time of day child wakes up in the morning: weeknights \_\_\_\_:\_\_\_\_ am/pm

weekends \_\_\_\_:\_\_\_\_ am/pm

|                                                           | Usually
(5-7times
/Week) | Sometimes
(2-4 times
/Week) | Rarely
(0-1 times
/Week) |
|-----------------------------------------------------------|--------------------------------|-----------------------------------|--------------------------------|
| 39.Child wakes up by him/herself                          |                                |                                   |                                |
| 40.Child requires alarm clock to wake up                  |                                |                                   |                                |
| 41. Child wakes up in negative mood                       |                                |                                   |                                |
| 42.Adults or siblings wake child up                       |                                |                                   |                                |
| 43.Child has difficulty getting out of bed in the morning |                                |                                   |                                |
| 44.Child takes a long time to be alert in the morning     |                                |                                   |                                |
| 45.Child wakes up very early                              |                                |                                   |                                |
| 46.Child has poor appetite in the morning                 |                                |                                   |                                |

## DAYTIME SLEEPINESS:

|                                                                                                    |            |             |              |
|----------------------------------------------------------------------------------------------------|------------|-------------|--------------|
| 47. Child show signs of napping during the day                                                     |            |             |              |
| 48.Child suddenly fall asleep during activities?                                                   |            |             |              |
| 49. Child appear fatigued                                                                          |            |             |              |
| 50. In the past week, has the child been very sleepy or fallen asleep in the following situations? |            |             |              |
|                                                                                                    | Not sleepy | Very sleepy | Falls asleep |
| Watching TV                                                                                        |            |             |              |

## Sleep Time

Weekday Sleep Time = Weekday morning wake-up time - night fall-asleep time

Weekend Sleep Time = Weekend morning wake-up time - night fall-asleep time

Average Sleep Time = (Weekday Sleep Time × 5) + (Weekend Sleep Time × 2) / 7

## Score Entry:

When entering the score for each question,

1= Occasionally (0 times/week to 1 time/week.) OR Not sleepy

2 = Sometimes (2 times/week to 4 times/week) OR Very sleepy

3= Usually (5 times/week to 7 times/week) OR falls asleep

## Score Conversion:

Higher scores indicate a higher risk of sleep problems. The conversion method for questions 1, 2, 3, 10, 11, and 26 is as follows: 1 = 3, 2 = 2, 3 = 1 (i.e., convert an original score of 1 to 3, keep a score of 2 unchanged, and convert a score of 3 to 1).

For questions 4, 5, 6, 7, 8, 9, 12, 13, 14, 15, 16, 17, 18, 19, 20, 21, 22, 23, 24, 25, 27, 28, 29, 30, 31, 321, and 322, the original input values remain unchanged."

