### Autism Treatment Evaluation Checklist (ATEC)

ATEC is developed by the Autism Research Institute and designed as a one-page checklist. Comprising 77 items, the ATEC has been utilized to assess the efficacy of interventions by measuring changes in response to various treatment modalities for children with ASD. The ATEC consists of four subscales totaling 77 items:

- Scale I: Speech, Language, and Communication (14 items, with scores ranging from 0 to 28)
- Scale II: Sociability (20 items, with scores ranging from 0 to 40)
- Scale III: Sensory and Cognitive Awareness (18 items, with scores ranging from 0 to 36)
- Scale IV: Health, Physical Condition, and Behavior (25 items, with scores ranging from 0 to 75)

Each category within the ATEC utilizes a four-point rating scale to gauge the severity of issues, ranging from 0 (indicating no problem) to 3 (indicating a serious problem). The ATEC generates a total score ranging from 0 to 179, with higher scores indicating a greater degree of reported activity limitations. This comprehensive assessment tool enables researchers and clinicians to gain insight into the challenges faced by individuals with ASD and to monitor changes in symptoms and functioning over time. For this study, the ATEC will be administered twice (pre- and post-tPCS) and carried out by an experienced therapist or doctor who is blinded regarding the subject allocation.

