### **4 Children's Sleep Habits Questionnaire (CSHQ)**

The Children's Sleep Habits Questionnaire (CSHQ) is a retrospective assessment tool to investigate sleep patterns in young children consisting of 45 items designed for parents to report on their child's sleep behavior. The CSHQ covers various sleep domains, including bedtime behavior and sleep onset; sleep duration; anxiety around sleep; behavior occurring during sleep and night wakings; sleep-disordered breathing; parasomnias; and morning waking/daytime sleepiness. Each item is rated on a three-point scale: "usually" if the behavior occurred five to seven times per week, "sometimes" for two to four times per week, and "rarely" for zero to one time per week. In this study, the CSHQ will be administered twice (pre- and post-tPCS) by experienced therapists who is blinded regarding the subject allocation through interviewing parents or caregivers in clinic.

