## Result Evaluation:

A total score higher than 41 on the Children's Sleep Habits Questionnaire (CSHQ) indicates poor sleep

00 quality.

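### The CSHQ scoring key in Appendix 3 does not fit the appended form: read by the form's item numbers it scores seven items backwards and leaves items 32–50 without a rule

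*Combined protocol and SAP*

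**What the plan says.** Section 2.3 makes change in CSHQ total and subdomain scores the outcome for the sleep objective. Section 4.3 (note on the CSHQ) describes an instrument "consisting of 45 items designed for parents". The form in Appendix 3 is numbered 1 to 50.

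Under Score Entry, Appendix 3 codes the rarest frequency as 1 and the most frequent as 3. Score Conversion says that higher totals mean more risk of sleep problems, and then: "The conversion method for questions 1, 2, 3, 10, 11, and 26 is as follows", with 1 and 3 exchanged. It leaves unchanged items 4–9, 12–25, 27–31 and two entries labelled 321 and 322. Result Evaluation adds: "A total score higher than 41 on the Children's Sleep Habits Questionnaire (CSHQ) indicates poor sleep" quality.

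Three items on the form show the mismatch. The key reverses "10. Child struggles at bedtime (cries, refuse to stay in bed etc" and "26. Child has physical aches and pain during sleep", and leaves "16. Child sleeps the right amount" as entered.

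Two smaller scoring statements are also at issue. Appendix 3 gives "Average Sleep Time = (Weekday Sleep Time × 5) + (Weekend Sleep Time × 2) / 7". For the ATEC, section 4.3 says "Each category within the ATEC utilizes a four-point rating scale to gauge the severity of issues", from 0 to 3, while listing scale maxima of 28, 40, 36 and 75 and a total of 179.

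**The concern.** A key that reverses a problem item, or fails to reverse a favourable one, counts improvement on that item as deterioration. Items scored the wrong way subtract from the change shown by the others, so a real effect on the total shrinks. A subdomain that holds several such items could be hit harder.

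The key is also incomplete for this form, so someone must decide later which items to score and how. Section 8.2 has two people at each of eight sites entering data from the paper forms, and section 12 promises release of participant-level data and code. Scoring should not rest on local or after-the-fact choices.

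**Working it through.** **The one score range that the plan states.** For the ATEC, section 4.3 gives 14, 20, 18 and 25 items. The form in Appendix 1 offers three options on Scales I–III (0–2) and four on Scale IV (0–3):

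14×2 + 20×2 + 18×2 + 25×3 = 28 + 40 + 36 + 75 = 179.

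This reproduces every stated maximum and the total. The four-point sentence is what disagrees. The plan states no CSHQ range, so the rest is an item-by-item count.

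**Size of the CSHQ key.** Reversed: 1, 2, 3, 10, 11, 26, which is 6. Unchanged: 4–9 (6), 12–25 (14), 27–31 (5), 321 and 322 (2), which is 27. Total 6 + 27 = 33. Without 321 and 322, 31 entries match a form item. Form items 32–50 (19 items) have no rule, among them item 38, which is a duration and not a frequency.

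**Direction of each keyed item on the printed form.**
- Reversed and favourable, so correct: 1, 2, 3.
- Reversed but a problem, so backwards: 10 (struggling at bedtime), 11 (fear of the dark), 26 (aches during sleep).
- Unchanged but favourable, so backwards: 8 (goes to bed willingly), 16 (right amount of sleep), 17 (good quality), 18 (steady quality).
- Items 23 and 24 (sharing the parents' room or bed) could be read either way and are not counted as backwards.

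That makes 3 + 4 = 7 backwards: 7/33 = 21% of the key, or 7/31 = 23% of the entries that exist on the form.

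The key also contradicts itself on this form. Items 8 and 9 are opposites scored the same way, as are 14 and 16. Items 11 and 12 are both bedtime fears scored in opposite directions.

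**Effect on the total.** Each backwards item gives 3 instead of 1 for a child without the problem, and 1 instead of 3 for a child with it. That is 7×2 = 14 points at each end.
- 31 matching items: no problems, 31 + 14 = 45 instead of 31; worst, 93 − 14 = 79 instead of 93.
- 33 entries, taking 321 and 322 as correctly keyed: 33 + 14 = 47 instead of 33; 99 − 14 = 85 instead of 99.

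So on the literal key a child with no sleep problem is already above 41.

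**Effect on change.** If a share p of the true change in the total falls on the seven items, the keyed total shows (1 − p) − p = 1 − 2p of it. The documents do not give p.
- Equal shift on every item (assumption): p = 7/31, so (31 − 14)/31 = 55%; with 33 entries, (33 − 14)/33 = 58%.
- No change on the seven items: p = 0, no loss.
- Half of all change on the seven items: p = 0.5, nothing visible.

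These are fractions of the raw mean change. The loss in power also depends on the variance of the mis-keyed total, which the documents do not give.

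**Average sleep time.** Take 9 h on weekdays and 10 h at weekends, for illustration. As printed: 9×5 + (10×2)/7 = 47.9 h. With brackets: (45 + 20)/7 = 9.3 h.

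**The case against.** The strongest reply is that the key plainly belongs to a differently numbered version. Its 33 entries and the labels 321 and 322 do not fit this form, so a careful coder would stop rather than reverse item 10, and seven items scored backwards would never occur. That explains the error but does not cure it: the documents contain no other key, and this one is written as an instruction. It does limit the claim. The documents do not show how any score was actually computed.

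Text extraction may have damaged parts of Appendix 3: question 50 shows one row, and the sleep-time bracket could have been lost. It would not explain a key that names the wrong items.

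It is also fair to say that neither the cut-off of 41 nor average sleep time feeds a planned analysis, since the endpoint is change in mean scores. And the mis-keying applies to both arms, so it shrinks a true difference without creating a false one.

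On the ATEC, the stated ranges and the three-option form settle the 0–2 rating despite the four-point sentence. Section 4.3 also fixes the direction, with higher meaning greater limitation.

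**Conclusion.** The point holds for the CSHQ. Applied by the form's own numbering, the key scores seven items backwards, names two items that do not exist, and omits items 32–50. The item count is 33 in the key, 45 in section 4.3 and 50 on the form. Under an equal shift across items, the secondary sleep outcome would show about 55% of its true change (58% on 33 entries). Subdomain scores could be distorted further, but by how much cannot be worked out because no item-to-subdomain map is given.

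Four stronger readings are tempting and not supported:
- That the sleep result would reverse sign. The seven items taken alone would move the wrong way, but the total reverses only if more than half of all change sits on them. Across the full range it still falls, from 79 to 45 on the matching items.
- That every child would be classed as a poor sleeper. This assumes that all form items are summed, which no section says, and the plan does not state which total the 41 belongs to.
- That the ATEC total could reach 77×3 = 231. The form offers no fourth option on Scales I–III.
- That the primary outcome would be mis-scored. What remains there is one contradictory sentence, plus an unstated reversal for Scales I and III, whose items are favourably worded although a higher total means worse.

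**What to change.** In Appendix 3:
- Replace the key with one written to the printed item numbers, listing which items are scored and the subdomain of each.
- Reverse only the favourably worded items that are scored: 1, 2, 3, 8, 16, 17, 18 and 39. State the direction chosen for 23 and 24.
- Reconcile 33, 45 and 50 items with section 4.3, and say which total the cut-off of 41 applies to.
- Write average sleep time as [(weekday × 5) + (weekend × 2)] / 7.

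In section 4.3, correct the ATEC sentence to 0–2 for Scales I–III and 0–3 for Scale IV. State that Scales I and III are scored N = 2, S = 1, V = 0, so that higher means worse.

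Rescore any data already entered from the item-level forms, using one common syntax for all sites. The cost is an appendix and syntax correction plus that rescoring. No new data are needed.
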